## Abstract

**Introduction:**

There is increasing interest in the relationship between acute infections and acute cardiovascular events. Most previous research has focused on understanding whether the risk of acute cardiovascular events increases following a respiratory tract infection. The relationship between urinary tract infections (UTIs) and acute cardiovascular events is less well studied. Therefore, the aim of this study is to determine whether there is a causal relationship between UTI and acute myocardial infarction (MI) or stroke.

**Methods and analysis:**

We will undertake a self-controlled case series study using linked anonymised general practice, hospital admission and microbiology data held within the Secure Anonymised Information Linkage (SAIL) Databank. Self-controlled case series is a relatively novel study design where individuals act as their own controls, thereby inherently controlling for time-invariant confounders. Only individuals who experience an exposure and outcome of interest are included.

We will identify individuals in the SAIL Databank who have a hospital admission record for acute MI or stroke during the study period of 2010–2020. Individuals will need to be aged 30–100 during the study period and be Welsh residents for inclusion. UTI will be identified using general practice, microbiology and hospital admissions data. We will calculate the incidence of MI and stroke in predefined risk periods following an UTI and in ‘baseline’ periods (without UTI exposure) and use conditional Poisson regression models to derive incidence rate ratios.

**Ethics and dissemination:**

Data access, research permissions and approvals have been obtained from the SAIL independent Information Governance Review Panel, project number 0972. Findings will be disseminated through conferences, blogs, social media threads and peer-reviewed journals. Results will be of interest internationally to primary and secondary care clinicians who manage UTIs and may inform future clinical trials of preventative therapy.

STRENGTHS AND LIMITATIONS OF THIS STUDYThe self-controlled case series method controls for time-invariant confounding, enabling more reliable causal estimates of the association between urinary tract infection (UTI) and acute myocardial infarction (MI) or stroke, compared with between-individual study designs.A causal relationship between UTI and acute MI or stroke has implications for our understanding of cardiovascular disease mechanisms and may inform new methods of disease prevention.Using individual-level population-scale anonymised, routinely collected electronic health record (EHR) data provides adequate power to study subgroups and maximises representativeness and generalisability.EHR data are collected and recorded for clinical purposes, and therefore, the reliability of research findings is dependent on the quality and completeness of these data.Clinical and microbiological diagnoses of UTI are subject to caveats, and therefore, we will use several definitions of UTI that use the different data sources in the Secure Anonymised Information Linkage Databank.

## Introduction

Since the late 1990s, an increasing number of observational studies have found an association between acute infections and myocardial infarction (MI).^1–10^ Most studies focused on respiratory tract infections (RTIs), and found an increased risk of acute MI in the 1–3 days following an RTI, with the effect size varying according to the infecting organism.^2–8^ For example, Kwong *et al* found a sixfold increase in the risk of MI in the week after influenza infection, a fourfold increase after respiratory syncytial virus and a threefold increase after other respiratory viruses.^5^ Several studies have also found evidence of an association between pneumonia and acute cardiovascular events (including MI and stroke).^9–13^ The increased risk of acute cardiovascular events following pneumonia infection persists for up to 10 years.^9^ This long-term risk of acute cardiovascular events has also been observed after other severe infections, including sepsis and bacteraemia.^14–17^

It is thought that acute infection may cause major cardiovascular events through three mechanisms. First, the inflammatory response from acute infection may destabilise atherosclerotic plaques. Second, the prothrombotic, procoagulant state associated with acute infection may increase the risk of thrombosis at the site of plaque disruption. Third, inflammation and fever lead to an increase in heart rate, which may cause ‘demand ischaemia’ if the metabolic demands of the myocardial cells exceed oxygen supply.^1^

Urinary tract infections (UTIs) can affect any part of the urinary system, including the kidneys, ureters, bladder and urethra. Most infections involve the lower urinary tract: the bladder and the urethra. UTIs are common infections, with 37% of women reporting experiencing at least one in their lifetime, and 29% experiencing more than one.^18^ UTIs are associated with considerable morbidity. The global burden of disease study 2010 estimates the disability-adjusted life-years attributable to tubulointerstitial nephritis, pyelonephritis and UTI to be 45 (95% uncertainty interval 32–55) per 100 000 population.^19^

The relationship between UTIs and acute cardiovascular events is less well studied than for RTIs. Only one previous study has examined this relationship. Smeeth *et al* used the self-controlled case series (SCCS) method to analyse data from the General Practice Research Database. They found increased rates of MI and stroke subsequent to UTI, with the risk being highest in the first 3 days.^6^ However, the data analysed are almost 20 years old, and there have been no attempts to replicate the findings. Furthermore, the study defined UTI using clinical codes only, so it is unclear if the reported associations related to individuals with clinical symptoms alone, or symptoms and bacteriuria, making it difficult to interpret whether individuals had true UTIs, or whether non-specific symptoms were misdiagnosed as UTI but represented early signs of a cardiovascular event. In addition, other studies have found that roughly two-thirds of women suspected to have UTI on presentation to primary care have no evidence of UTI on microbiological culture.^20^ Therefore, the use of clinical codes alone to define UTI may lead to bias from misclassification of the exposure.

Therefore, the aim of this study is to determine whether there is a causal relationship between UTI and acute MI or stroke by analysing linked general practice, hospital admission and microbiology data, from a representative sample of the Welsh population. We will use the SCCS method, which controls for time-invariant confounding, enabling us to more reliably draw causal inferences between UTI and acute MI or stroke, compared with between-individual study designs.

## Methods and analysis

### Aims and objectives

The specific objectives of this research are to:

Estimate incidence rate ratios (IRRs) for acute MI and stroke in the 90 days following a clinically suspected and microbiologically confirmed UTI compared with baseline (all times outside of the 90-day risk period).Assess the effect of different methods of UTI ascertainment on estimated rate ratios (ie, clinically suspected and microbiologically confirmed; clinically diagnosed only; clinically suspected but not supported by microbiology and UTI diagnosed and treated in hospital).Investigate whether the effect of a clinically suspected and microbiologically confirmed UTI on acute MI and stroke differs according to the infecting organism.

Our primary hypothesis is that a clinically suspected and microbiologically confirmed UTI will increase the risk of acute MI or stroke in the 0–90 days postinfection period.

### Data

We will use the Secure Anonymised Information Linkage (SAIL) Databank. This is an internationally recognised trusted research environment (TRE), with robust secure storage, enabling access to anonymised, linkable, individual-level Welsh population-scale data for research, with a focus on improving population health and health services. Data within SAIL are pseudonymised and made available to approved projects and users following an application to, and approval from the independent information governance review panel (IGRP). SAIL’s storage and linkage processes ensure anonymity: first, data sources being provided to SAIL are split as per the standard split file process, with the source organisation splitting the source data into demographic data and clinical data, with a system linkage field to allow data to be rejoined later. This addresses confidentiality and disclosure issues that arise when working with health data by separating easily recognised person-based variables such as name and date of birth from clinical data, including information on diagnoses, tests and prescriptions. The demographic data are anonymised and assigned an anonymised linkage field. These split files are then joined together using the system linkage field by the SAIL team and made available to researchers following encryption.^21–23^

We will use the SAIL Databank to access the following linked data: Welsh Longitudinal General Practice data (WLGP), Patient Episode Database for Wales (PEDW), Welsh Results Reporting Service (WRRS). The WLGP contains data from 84% of general practices in Wales, consisting of longitudinal data for 2.6 million Welsh residents, representing 84% of the population.^24^ Demographic data, clinical diagnoses and prescription data are included. The PEDW contains International Classification of Disease version 10 (ICD-10) coded diagnoses for admissions to any Welsh hospital.^25^ The WRRS contains data on all tests requested from primary and secondary care National Health Service (NHS) Wales organisations processed and analysed in NHS Wales laboratories, including requests for urine microscopy, culture and antibiotic susceptibilities.^26^ Data are available from the data sources at varying times based on when clinical information systems began, with data quality improving over time. As such, for our study, based on our approvals and where the data sources have consistent coverage and quality, we will be using them between 1 January 2010 and 31 December 2020.

### Study design

Individuals who experience UTIs and individuals who do not can differ in unmeasured ways and hence could be sources of residual confounding. We will use the SCCS design method to deal with this issue. The SCCS method is an epidemiological study design for which individuals act as their own control so that both measured and unmeasured characteristics that vary between individuals are completely controlled.^27^ Only individuals who have experienced an outcome and exposure of interest are included. The SCCS method compares the incidence of an outcome during predefined risk periods with incidence during baseline periods (all times outside of risk and prerisk periods) and estimates the temporal association between a transient exposure and outcome. Time-invariant covariates (eg, sex) are inherently controlled for, and time varying covariates (eg, age) are adjusted for within the models. The method was originally developed to investigate associations between vaccinations and acute adverse events, such as aseptic meningitis,^28 29^ but has since been applied in a range of epidemiological settings,^30–32^ including non-acute events such as autism.^33^ As with other study designs, the SCCS method makes several assumptions that need to be met in order to obtain valid and unbiased estimates, but there are model extensions which provide solutions to violations of these assumptions under certain circumstances.^34^ The model assumptions, how they apply to our study, and the solutions to violations of the assumptions are given in table 1.

**Table 1 T1:** Model assumptions and solutions to violations of those assumptions

Assumption	How the assumption applies to this study	Solution	Example of use of the solution in the literature
Subsequent exposures should not be affected by previous events.	We might see a temporary increase in UTIs subsequent to an MI or stroke event, which would bias estimates towards the null.	Apply a prerisk period.	Gibson *et al* studied the association between prescription drugs and road traffic accidents. As some drugs may be used to treat anxiety or pain caused by the crash, a 4-week pre-exposure period was included.^37^
	As both MI and stroke have relatively high death rates, the length of the observation period is dependent on events, and no further exposures are possible after death.	Use an event-dependent observation period model extension^38^ and conduct a sensitivity analysis that repeats the analysis, excluding individuals who died within 30 days of the event.	Bruer *et al* used the event-dependent observation period model extension in their study on the association between antipsychotic drugs and myocardial infarction.^39^ Langan *et al* studied the risk of stroke following herpes zoster. They conducted a sensitivity analysis excluding individuals who died within 90 days of stroke.^40^
Event rates are constant within defined periods	MI and stroke are more common in older individuals and may be affected by seasonal changes.	Control for age and season effects.	Grave *et al* studied the association between seasonal influenza vaccination and Guillain-Barré syndrome. They adjusted for calendar month, as the vaccinations are seasonal by design.^41^ In a study of the association between chickenpox and stroke, Thomas *et al* adjusted for age in 5-year age bands.^42^
Events are independently recurrent or rare.	MI and stroke are not independent: once an individual has a first event, they are more likely to have a second.	Study first events only.	Langan *et al* began the observation period 12 months into follow-up time to ensure first stroke events had been correctly identified.^40^

MI, myocardial infarction; UTIs, urinary tract infections.

A diagrammatic representation of observation time for an individual in the proposed SCCS design is given in figure 1. Risk periods start on the date of an UTI and end 90 days later. The date of an UTI is the earliest date of occurrence of any of the events necessary for each different UTI definition. For example, the definition of UTI in our primary analysis is a combination of an UTI-related diagnostic code and antibiotic prescription in WLGP data and a urine culture result that supports a diagnosis of UTI in the WRRS data, occurring within a 7-day window. In this case, the date of the UTI would be the date of whichever of the following events occurred first: UTI-related diagnostic code, antibiotic prescription, supporting urine culture.

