**Figure 1 F1:**
[figure not shown]
Diagrammatic representation of observation time for an individual in the proposed self-controlled case series design. MI, myocardial infarction; UTI, urinary tract infection.

Individuals can have more than one UTI during the observation period, and therefore can have more than one 90-day risk period. Where risk periods overlap, the later period takes precedence, and the earlier period is shortened. There will be a prerisk period of 7 days before the risk period, to allow for the situation where an individual has an UTI for several days prior to consultation, so events in the prerisk period are not erroneously attributed to the baseline period.

Baseline periods are all times outside of the risk and prerisk periods. The study period is from 1 January 2010 to 31 December 2020. The observation period is different for each individual. It generally follows the study period but may start later for some individuals who were not Welsh residents at the start of the study period but became so later, or who turned 30 years of age sometime during the study period. Similarly, the observation period may end before the study period when individuals moved out of Wales or died.

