### Outcomes

Outcomes of interest are acute MI or stroke, as identified by ICD-10 codes from inpatient diagnoses recorded in the PEDW. A list of ICD-10 codes to be used are given in online supplemental material A.

10.1136/bmjopen-2022-064586.supp1Supplementary data

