### Sensitivity and subgroup analyses

We will perform several sensitivity and subgroup analyses to assess the robustness of the findings of our primary analysis to different assumptions:

We will explore the impact of using a wider definition of MI and stroke, including ICD-10 codes for acute coronary syndromes and transient ischaemic attacks. This will include events that have potentially been missed by our main definition and assess how sensitive our findings are to the definition of MI and stroke.We will explore the impact of widening the microbiological definition of UTI to bacterial growth of a single organism of ≥1x10^7^ CFU per litre irrespective of WCC.We will differentiate first-ever MI or stroke from recurrent events, and report risk estimates separately. This analysis will exclude individuals with a PEDW record of an event before the observation period, and include only those who have their first ever event during the observation period.We will extend the prerisk period to 14 days. Some individuals may have had an UTI for several days prior to diagnosis, and so an acute MI or stroke during this time may relate to exposure but without a prerisk period, would count towards the baseline period.We will repeat the analysis excluding individuals who died within 30 days of an event to examine the potential effect of an event dependent observation period.We will restrict the definition of UTI to include only antibiotic prescriptions for nitrofurantoin (currently recommended first-line therapy) to explore whether the choice of antibiotic impacts the findings.We will use interaction terms to assess the impact of specific bacterial organisms on the relationship between UTI and MI or stroke.We will examine whether the COVID-19 pandemic may affect our findings by (1) excluding individuals whose MI or stroke occurred in 2020, and (2) including an interaction term to explore whether the association between exposure and outcome differs in 2020 vs pre-2020.We will include an interaction term to explore whether the association between exposure and outcome differs in those with and without a history of diabetes, given its potential role as a risk factor of both UTI and MI/stroke.

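### The prerisk period is Table 1's only remedy for a rise in UTIs after MI or stroke, but its 7 days (14 in sensitivity) are justified by consultation delay and may be too short for that purpose

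*Protocol article*

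**What the plan says.** In the protocol article, Table 1 (Study design) takes up the assumption that events do not affect later exposures. It warns: "We might see a temporary increase in UTIs subsequent to an MI or stroke event, which would bias estimates towards the null". The remedy in that row is "Apply a prerisk period", with no length given. The row's literature example concerns prescription drugs and road crashes, where "a 4-week pre-exposure period was included".

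The length is set in the text below Figure 1: "There will be a prerisk period of 7 days before the risk period". The reason given is "to allow for the situation where an individual has an UTI for several days prior to consultation", and the Exposure section repeats it. Under Sensitivity and subgroup analyses the plan adds "We will extend the prerisk period to 14 days", again because a UTI may precede its diagnosis by several days.

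Three further statements matter:
- Outcomes are MI or stroke "as identified by ICD-10 codes from inpatient diagnoses recorded in the PEDW".
- The primary UTI definition (Exposure, Table 2) needs a GP UTI code, a GP antibiotic prescription and a supporting culture within 7 days.
- The text after Table 2 notes that in the primary analysis a UTI diagnosed in hospital will probably fall in baseline time.

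**The concern.** One window serves two purposes. Delay before consultation is a matter of days. A rise in UTIs after an acute admission lasts for however long the admission and recovery raise the risk, and the protocol does not state that duration. No section ties the 7 or 14 days to it.

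If a patient has an MI or stroke and a qualifying UTI is dated more than 7 days later, the event falls outside the prerisk window and is counted in baseline. A temporary excess of such UTIs inflates baseline incidence and lowers the IRR, which is towards the null when the true IRR exceeds 1. The data sources may sharpen this: the window covers the first days after an admission, when a GP code and GP prescription are less likely to be generated.

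At stake are a modest underestimate of the main IRR, some loss of power, and the lack of a planned analysis that would show whether the bias named in Table 1 remains.

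**Working it through.** **Inputs from the protocol article**
- Cases: 51,656 MI and 58,146 stroke; 10% exposed; 90-day window; IRR 1.3; alpha 0.05, taken as two-sided (Sample size and power).
- Mean observation (Summary of cases), weighted by sex. Stroke: 0.49 × 2981 + 0.51 × 2796 ≈ 2,887 days (2,888 used below; one day makes no difference at two decimals). MI: 0.63 × 3251 + 0.37 × 2981 ≈ 3,151 days.

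**The plan's own figure: 90% power**

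The signed-root likelihood-ratio formula for case series, without age effects, has r = 90/T and d = 1.3r + 1 − r:
- A = 2[(1.3r/d) ln 1.3 − ln d]
- B = (ln 1.3)² × 1.3r(1 − r)/(A d²)
- exposed cases needed = (1.960 + 1.282√B)²/A

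MI (T = 3,151): A = 0.002254, B = 1.083, so 4,813 exposed or 48,133 cases are needed; power with 51,656 is 0.919. Stroke (T = 2,888): A = 0.002450, B = 1.082, so 4,427 exposed or 44,270 cases are needed; power with 58,146 is 0.959. The stated 90% is reproduced.

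**Bias left by a short prerisk window**

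The documents do not give these quantities, so they are assumed:
- k = multiplier on the UTI rate after the event
- D = last day of the rise
- L = initial days with no GP-recordable UTI (0 to 14)

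With prerisk length p and one UTI per person:
- excess baseline days E = (k − 1)(D − max(L, p)) − max(0, L − p)
- baseline days b = T − 90 − p
- observed IRR = 1.30/(1 + E/b)

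Worked case, k = 3, D = 90, L = 0, T = 2,888:
- p = 7: E = 2 × 83 = 166, b = 2,791, IRR = 1.30/1.0595 = 1.227
- p = 14: E = 2 × 76 = 152, b = 2,784, IRR = 1.233
- p = 28: E = 2 × 62 = 124, b = 2,770, IRR = 1.244
- p = 90: E = 0, IRR = 1.300

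With L = 14 and p = 7: E = 2 × 76 − 7 = 145, IRR = 1.236. Moving to p = 14 then gives 1.233, slightly further from the truth.

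Range over T = 2,888 to 3,151 and L = 0 to 14:

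| Assumed rise | p = 7 or 14 | p = 28 | p = 90 |
|---|---|---|---|
| doubled to day 90 | 1.26–1.27 | 1.27 | 1.30 |
| tripled to day 90 | 1.23–1.24 | 1.24–1.25 | 1.30 |
| tripled to day 30 | 1.28–1.29 | 1.30 | 1.30 |
| tripled to day 180 | 1.16–1.18 | 1.17–1.18 | 1.22–1.23 |

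A direct fit of the case-series likelihood to the implied event distribution (T = 2,888) agrees with the formula to within about 0.001; for the tripling to day 90 with L = 0 it gives 1.228 at 7 days and 1.234 at 14.

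**Effect on power:** at an attenuated IRR of 1.26, power is about 0.84 (MI) and 0.90 (stroke); at 1.23, about 0.75 and 0.83.

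**The case against.** A reader might infer that the prerisk period cannot remove the rise because GP-recorded UTIs mostly follow discharge. The documents do not support that. They give neither length of stay nor event-to-UTI timing, and Table 1 says only that a temporary rise might occur. A UTI is dated from its earliest component (Study design), and the laboratory data include secondary-care samples (Data). A culture taken in hospital can therefore date a primary-definition UTI inside the window, and short stays act the same way. Secondary analyses 4 and 5 also count hospital UTIs, so the data-source argument applies mainly to the GP-based definitions. All of this stands: the window removes part of the rise, and how much is unknown.

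The 4-week example sets no standard for UTI after MI or stroke, and 28 days would do little better than 7 if the rise lasted to day 90. That stands too. So does the point that the bias is conservative for a hypothesis of increased risk, although a conservative bias makes a null or weak result harder to read.

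The 14-day analysis is offered as a check on diagnostic delay, so it does not fail at its stated task. The Statistical analysis section already estimates an IRR for the prerisk period. But that covers only the first days after the event, and neither analysis tests the bias that Table 1 names.

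A reader might also add that Table 1's "Use an event-dependent observation period model extension" is not repeated in the analysis sections. That remedy answers a different problem, death ending observation. Table 1 is part of the methods and prescribes it, and an article need not say it twice. It is no part of this point.

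**Conclusion.** The point holds in a limited form. The prerisk length is not justified for the purpose Table 1 gives it and may be too short. Any part of a post-event rise that outlasts the window stays in baseline and lowers the IRR.

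The loss is modest because baseline is about 2,800–3,050 days per case. From a true 1.30 it is about 2–3% for a doubling to day 90, about 5% for a tripling to day 90, and 1–2% for a tripling that ends by day 30. These figures rest on assumed size, duration and early gap, with one UTI per person. The mismatch between purpose and length is certain from the text; the size of the bias is conditional. In these scenarios, moving from 7 to 14 days shifts the estimate by about 0.01 or less, so agreement between the two runs would say nothing about whether this bias is present.

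**What to change.** 1. Before fitting the outcome models, tabulate or plot the interval from event to next qualifying UTI, separately for MI and stroke, and state how the prerisk length relates to it.
2. Split pre-UTI time into strata, for example 1–7, 8–28 and 29–90 days before the UTI, and report an IRR for each. A raised IRR in the later strata would show an excess that the 7-day window leaves in baseline.
3. Beside the 14-day run, add sensitivity analyses with longer prerisk windows, including 90 days. A 28-day run alone would not suffice if the rise lasts to day 90.
4. State both purposes of the prerisk period where its length is set.

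The cost is a few more model runs on data already held. Going from 7 to 90 days takes 83 days per UTI out of baseline: 83/2,791 = 3.0% for stroke and 83/3,054 = 2.7% for MI, and more for people with several UTIs.
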